## Update

### Introduction

Acute Upper Gastrointestinal Bleeding (AUGIB) is the most common reason for emergency hospital admission with a gastrointestinal disorder in the United Kingdom (UK) with an annual incidence of 50 to 150/100,000 adults [1]. It is also the leading indication for red blood cell (RBC) transfusion, accounting for 14% of all RBCs transfused in England [2]. RBC transfusion is commonly based upon the patient’s haemoglobin (Hb) level; however, the optimal Hb threshold at which to transfuse is unclear [3,4]. Two observational studies have indicated an association between RBC transfusion after AUGIB and risk of further bleeding and mortality [5,6]. A recently published randomised trial found a liberal approach to transfusion led to an increased risk of mortality [7], although these results may not be generalisable due to the strict protocols of care implemented in this single centre trial, which are unlikely to be reproducible in most healthcare institutions.

The Transfusion in Gastrointestinal Bleeding (TRIGGER) trial is a cluster-randomised trial designed to evaluate the feasibility of implementing a restrictive *vs.* liberal RBC transfusion policy for patients admitted to hospital with AUGIB [8]. TRIGGER is a pragmatic trial which aims to reflect real world settings as closely as possible. Six hospitals in the United Kingdom were randomised in a 1:1 ratio to follow either a liberal transfusion policy (where eligible patients are transfused when their Hb drops below 10 g/dL) or a restrictive transfusion policy (where eligible patients are transfused when their Hb drops below 8 g/dL). Randomisation was performed using permuted blocks without stratification or matching, with a block size of six (to ensure three hospitals in each arm). Hospitals were randomised in July 2012, and recruitment took place between September 2012 and March 2013.

The TRIGGER protocol has been published in Transfusion Medicine Reviews [8] (available at http://www.tmreviews.com), and gives details on the rationale for the study, the inclusion/exclusion criteria, the sample size calculation and the process for consenting patients to the trial. This update to the published protocol describes the statistical analysis plan for TRIGGER.

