### Clinical outcomes

Main analysis of the clinical outcomes will be by ITT, and will include all consented patients with a recorded Hb below 12 g/dL during follow-up, and for whom the outcome is available. Including only patients with a Hb <12 g/dL allows us to target those patients most likely to be affected by the treatment policy, resulting in a more powerful analysis on a more relevant patient population. A Hb of 12 g/dL was chosen as the cut-off point because it is likely that some patients will be transfused (against policy) above 10 g/dL; if the proportion of patients transfused above 10 g/dL differs between treatment arms, excluding these patients could lead to bias. Using a cut-off of 12 g/dL should allow the majority of transfused patients to be included in the analysis, leading to an unbiased comparison. A secondary analysis will include all consented patients, regardless of whether their Hb dropped below 12 g/dL.

Results will be considered statistically significant at the 5% level. Main analyses for clinical outcomes will be unadjusted for baseline covariates; however, a set of secondary analyses will be adjusted for patient age, the presence of shock, the number of major co-morbidities, and the presence of coagulopathy (defined as an international normalised ratio (INR) >1.5 or a prothrombin time (PT) >3 seconds greater than the control). Mean imputation within the centre will be used for patients with missing baseline covariates [11]. Patient age and the number of major co-morbidities (encompassing ischaemic heart disease, cardiac failure, liver disease, renal disease, respiratory disease, malignancy and stroke) will be modelled using fractional polynomials to allow for the possibility of a non-linear association [12]. Further bleeding up to Day 28 is regarded as the primary clinical outcome.

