### Adjusted analyses

Adjusted analyses using cluster-level summaries will be performed as follows [14]:

1) A regression model (linear for continuous outcomes and logistic for binary outcomes) will be fit to individual-level patient data, and will be adjusted for the baseline characteristics listed earlier (age, shock, presence of coagulopathy and the number of major co-morbidities). The model will not adjust for treatment effect, or for centre.

2) Predicted values based on the fitted regression model will be calculated for each patient (for binary outcomes this equates to the predicted probability of experiencing an event, for continuous outcomes this equates to the predicted mean).

3) The expected outcome in each cluster will be calculated. For binary outcomes, this is the expected number of events in each cluster, and is calculated by summing the predicted probabilities for each patient in that cluster. For continuous outcomes, the expected mean value is calculated by taking the mean of the predicted values in each cluster.

4) An appropriate residual is calculated for each cluster. For binary outcomes, this is the observed number of events minus the expected number of events, divided by the number of patients in the cluster. For continuous outcomes, this is the observed mean minus the expected mean.

5) A linear regression model will be fit using the residuals calculated above as cluster-level summaries, with only the treatment group as a covariate. No degrees of freedom correction will be made for performing an adjusted analysis, as only patient-level variables will be adjusted for.

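### With 3 v 3 unmatched hospitals and recruitment after allocation, the adjusted cluster-level analysis already specified is the better main analysis for further bleeding and mortality to Day 28

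*SAP article*

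**What the plan says.** The Introduction of the SAP article states: "Six hospitals in the United Kingdom were randomised in a 1:1 ratio". It adds: "Randomisation was performed using permuted blocks without stratification or matching, with a block size of six". On timing: "Hospitals were randomised in July 2012, and recruitment took place between September 2012 and March 2013". Every patient therefore entered after the hospital's policy had been assigned.

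Under Analysis principles, Clinical outcomes, the main analysis set "will include all consented patients with a recorded Hb below 12 g/dL during follow-up, and for whom the outcome is available". The choice of analysis follows: "Main analyses for clinical outcomes will be unadjusted for baseline covariates". Analyses adjusted for age, shock, number of major co-morbidities and coagulopathy are secondary. No reason is given for this order.

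The Adjusted analyses section sets out the adjustment in five steps. A patient-level model without treatment or centre gives expected outcomes. Observed minus expected is formed per hospital, and these six residuals are regressed on arm. On its cost the article says: "No degrees of freedom correction will be made for performing an adjusted analysis, as only patient-level variables will be adjusted for".

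The section on cluster-level summaries for feasibility outcomes treats the baseline profile of consented patients, and their difference from non-consented patients, as checks on selection bias.

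**The concern.** With three hospitals per arm and no restriction on case mix, hospitals will differ in the risk of the patients they admit. In an unadjusted analysis those differences feed into the between-hospital variance, which is estimated on only 4 degrees of freedom. Adjusting for patient-level prognostic factors takes part of that variance out.

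Because consent follows allocation, the kind of patient recruited could also differ between arms. Randomising hospitals does not protect against that. The plan intends to look for such differences but leaves their effect in the main estimate. The usual reason to avoid adjustment with so few clusters is the loss of scarce degrees of freedom, and by the plan's own account that does not arise here.

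At stake are the width of the interval and, if recruitment did differ on the measured factors, the position of the main estimate for the primary clinical outcome and for mortality.

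**Working it through.** **Inputs from the article.** Six hospitals, 3 v 3; one summary per hospital, equally weighted; "Results will be considered statistically significant at the 5% level", taken as two-sided because 95% intervals are reported. There is no stated figure to reproduce: event rate, intra-class correlation, cluster size and covariate strength are not given.

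**Design arithmetic.**
- Residual degrees of freedom: 6 − 2 = 4, so t = 2.776.
- 95% half-width = 2.776 × √(1/3 + 1/3) × s = 2.27 s, where s is the between-hospital SD of the summary.
- The arm difference in a hospital-mean covariate has SD √(2/3) = 0.816 between-hospital SDs. If normal, the chance that it exceeds one such SD is P(|Z| > 1.225) = 22%.

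**Simulation, set A** (assumed: 3,000 trials per scenario; one prognostic score with log-odds 0.8 per SD; hospital means of the score varying with SD 0.3; residual hospital log-odds SD 0.2; no treatment effect). The shift is the difference between arms in the score, in SDs, standing for differential recruitment. Each cell gives mean estimate / mean 95% half-width, both in percentage points, / rejection rate.

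| Patients per hospital, baseline risk | Shift | Unadjusted | Adjusted |
|---|---|---|---|
| 60, 7% | 0 | 0.1 / 9.4 / 5.0% | 0.1 / 8.2 / 4.9% |
| 60, 15% | 0 | −0.2 / 13.6 / 4.5% | −0.1 / 11.3 / 5.2% |
| 120, 7% | 0 | 0.0 / 7.5 / 4.4% | 0.0 / 6.1 / 5.3% |
| 120, 15% | 0 | 0.0 / 11.7 / 5.1% | 0.0 / 9.1 / 5.0% |
| 60, 7% | 0.3 | 2.1 / 9.9 / 6.5% | 0.0 / 8.6 / 3.9% |
| 60, 15% | 0.3 | 3.3 / 14.4 / 7.1% | 0.0 / 11.9 / 4.8% |
| 120, 7% | 0.3 | 2.0 / 8.1 / 7.7% | 0.0 / 6.6 / 4.7% |
| 120, 15% | 0.3 | 3.5 / 12.3 / 9.6% | 0.1 / 9.4 / 4.4% |

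With no shift, the half-width narrows by 12% (9.40 to 8.23) to 22% (11.67 to 9.06). With no case-mix variation between hospitals the gain is only 2 to 3% (for example 9.28 to 9.00). With a true effect of about 9 points and no shift (120 per hospital, 15% risk), power is 28% unadjusted and 43% adjusted.

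**Simulation, set B** (weaker assumptions: 1,500 trials; 120 per hospital; 10% baseline risk; five uninformative first-stage terms added).
- Slope 0.4, case-mix SD 0.2, residual SD 0.2: half-width 7.3 to 7.1, a gain of 3%.
- The same with residual SD 0.3: 8.8 to 8.4, a gain of 5%.
- Slope 0.8, case-mix SD 0.1, residual SD 0.1: 6.9 to 6.4, a gain of 7%.
- Slope 0.4, shift 0.2, case-mix SD 0.1, residual SD 0.2: unadjusted estimate 0.6 points with 5.3% rejection; adjusted −0.2 points with 5.4%.

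A further set at shifts of 0.2 to 0.3 SD gave an unadjusted bias of 1.2 to 2.6 points, removed by adjustment. Across its scenarios the adjusted analysis had a type I error of 4.0 to 6.9%.

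**Hand check of the bias.** To first order, bias ≈ slope × shift × p(1 − p).
- Set A, 7% risk: 0.8 × 0.3 × 0.07 × 0.93 = 1.6 points.
- Set A, 15% risk: 0.8 × 0.3 × 0.15 × 0.85 = 3.1 points.
- Set B: 0.4 × 0.2 × 0.10 × 0.90 = 0.7 points.

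The set A simulations lie somewhat higher because average risk over a spread of scores exceeds the baseline risk.

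**Limit of the remedy.** With a shift in an unmeasured factor of the same strength as 0.6 SD of the score (120 per hospital, 15% risk), bias was 7.3 points unadjusted and 7.1 adjusted, with rejection of 19.4% and 29.7%. Adjustment does not help there, and the narrower interval raises the false-positive rate.

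**The case against.** The strongest reply is that this is a choice, not an error. The unadjusted analysis is pre-specified, cluster-level summaries suit a trial with very few clusters, and the adjusted results will be reported anyway. The trial is a feasibility study, and with 4 degrees of freedom neither version is likely to settle a clinical question. All of that stands, and it limits the weight of the point.

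A reader might infer that an unmatched 3 v 3 design makes the unadjusted result invalid. It does not: under chance imbalance alone its type I error stayed near 5%. Some imbalance is to be expected, but a difference above one between-hospital SD on a given covariate has a chance of about 22%.

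A reader might also infer that recruitment was in fact selective. The article does not show that. It does not say that those seeking consent knew the policy; this can only be inferred from hospitals having been assigned one before recruitment. The plan also provides checks on selection.

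The size of the gain is open to challenge too. Under set B it is 3 to 7% in width, and the false-positive problem disappears. What survives is the direction, which favoured adjustment on width in every scenario run, and the absence of a cost in degrees of freedom.

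Finally, adjustment cannot become the main analysis for every clinical outcome. The adjusted procedure defines residuals for means and event counts only, whereas length of stay is summarised by the median. Rare events may not support a logistic first stage.

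**Conclusion.** The point holds in a limited form. Making the unadjusted comparison the main one gives up some precision and leaves any recruitment imbalance on measured prognostic factors in the headline estimate, although a suitable adjusted analysis is already written and keeps 4 degrees of freedom.

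On assumed inputs, the interval narrows by roughly 3 to 20%. A 0.2 to 0.3 SD shift in a measured risk score moves the unadjusted estimate by about 1 to 3 points, and the adjusted one by about 0. Individual scenarios fall slightly outside these rounded ranges. The figures depend mainly on how strongly the covariates predict outcome and how much hospitals differ on them, and the article gives neither.

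It would be too strong to say that adjustment would deal with selection generally. It acts only on measured covariates, and it does not repair selection on Hb recorded during follow-up, which defines the main analysis set. Nor is baseline Hb shown to be a necessary addition: no separate gain from it was calculated.

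**What to change.** In Analysis principles, Clinical outcomes, name the procedure in Adjusted analyses, with the four covariates already listed, as the main analysis for further bleeding and all-cause mortality up to Day 28. Report the unadjusted result beside it. Keep the unadjusted analysis as main for all other clinical outcomes, including rare events and length of stay. Fix this split in advance by named outcome, not by observed event counts, so that the main method cannot depend on the data. Make the change before outcome data are examined. Baseline Hb may be considered as a further pre-specified covariate.

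The cost is a change of wording, since the analysis and its covariates are already planned. The downside is small: the main result for these two outcomes would rest on a first-stage logistic model with fractional polynomial terms, and on mean imputation within centre where covariates are missing.

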### Cluster level summaries for feasibility outcomes

Cluster-level summaries for feasibility outcomes will be calculated separately in each centre as follows:

1) **Recruitment rate (patients consenting):** the proportion of eligible patients providing consent.

2) **Ineligible due to severity of bleeding:** the proportion of screened patients who are ineligible due to severity of bleeding

3) **Overall adherence:** the mean adherence rate per patient

4) **Adherence per patient:** the proportion of patients who had no protocol deviations

5) **Adherence per Hb count:** the proportion of Hb counts that did not lead to a protocol deviation

6) **Selection bias - baseline variables for consented patients:** The mean age, baseline Hb, number of major co-morbidities, clinical Rockall score and Blatchford score, and the proportion of patients with shock will be calculated for consented patients.

7) **Selection bias - difference between consented and non-consented patients in baseline variables:** The difference in the mean Rockall score and Blatchford score, and mean baseline Hb between consented and non-consented patients will be calculated in each centre.

8) **Red blood cell exposure (number of transfusions):** the mean number of RBC units transfused per patient.

9) **Red blood cell exposure (patients receiving at least one transfusion):** the proportion of patients who receive at least one RBC transfusion.

10) **Hb concentration up to Day 7, and over the entire in-hospital follow-up period, prior to discharge/death/Day28:** the area-under-the-curve will be calculated for each patient

11) **Hb concentration at discharge:** the mean Hb will be calculated

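### The secondary adjusted clinical analyses leave out baseline Hb, so an Hb imbalance that the four listed covariates do not explain would stay in the adjusted estimate if Hb predicts the outcome

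*SAP article*

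**What the plan says.** Under Analysis principles, Clinical outcomes, the SAP states that "Main analyses for clinical outcomes will be unadjusted for baseline covariates" and then that "a set of secondary analyses will be adjusted for patient age, the presence of shock, the number of major co-morbidities, and the presence of coagulopathy". Step 1 under Adjusted analyses repeats the list: the patient-level model "will be adjusted for the baseline characteristics listed earlier (age, shock, presence of coagulopathy and the number of major co-morbidities". The two lists agree, and neither includes baseline Hb or gives a reason for leaving it out.

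Hb has three other roles in the plan:

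- It defines both policies. The Introduction describes a "liberal transfusion policy (where eligible patients are transfused when their Hb drops below 10 g/dL" and a "restrictive transfusion policy (where eligible patients are transfused when their Hb drops below 8 g/dL" (units g/dL).
- It defines the main clinical analysis set, which is limited to consented patients with an Hb below 12 g/dL recorded during follow-up.
- It is a recruitment check. Under Cluster level summaries for feasibility outcomes, item 6 (labelled as selection bias) summarises "The mean age, baseline Hb, number of major co-morbidities, clinical Rockall score and Blatchford score, and the proportion of patients with shock" in consented patients. Item 7 compares baseline Hb and the two risk scores between consented and non-consented patients.

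The Introduction also says that six hospitals were randomised 1:1 in July 2012, without stratification or matching, and that recruitment ran from September 2012 to March 2013.

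**The concern.** Hospitals were allocated first and patients consented afterwards, with only three hospitals per arm and nothing in the design to balance case-mix. Presenting Hb could therefore differ between arms by chance or through selective recruitment. The plan would show such a difference through item 6, but no planned clinical analysis would remove it. Age, shock and co-morbidities appear both in the recruitment check and in the adjusted model. Baseline Hb appears only in the check.

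Lower presenting Hb plausibly marks a heavier bleed, though the documents give no figure for this. If it does, an adjusted difference in further bleeding or mortality could partly reflect how ill patients were on arrival. The adjusted set is the only clinical analysis in the plan that takes account of baseline differences, and the trial is meant to inform a phase III design.

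**Working it through.** **Text check.** The covariate lists under Clinical outcomes and Adjusted analyses both contain age, shock, number of major co-morbidities and coagulopathy. Baseline Hb is in neither. It is in items 6 and 7 of the feasibility summaries, so it is collected. There is no figure in the plan to reproduce.

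**Size by hand.** In a logistic model with risk p, an arm difference D in an omitted covariate with log odds ratio b per unit shifts the risk difference by about

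bias ≈ b × D × p(1 − p).

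This holds when the four listed covariates explain none of D. Assume p = 0.10, so p(1 − p) = 0.09. The odds ratio (OR) is per 1 g/dL lower Hb.

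| OR | b | D = 0.5 g/dL | D = 1.0 g/dL |
|---|---|---|---|
| 1/0.9 ≈ 1.11 | 0.105 | 0.47 points | 0.95 points |
| 1.25 | 0.223 | 1.00 points | 2.01 points |

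**Size by simulation of the plan's own procedure.** A logistic model was fitted without treatment or centre. The cluster residual was (observed − expected)/n, and the two arms were compared on six residuals with 4 degrees of freedom. Assumptions not in the documents: no true policy effect, 100 patients per hospital, event risk roughly 10%, Hb SD 2.5 g/dL, an Hb shift independent of the other covariates, no extra between-hospital variance, and 600 runs per setting. Each cell gives the absolute mean false effect in percentage points, over two assumed correlations of Hb with the severity behind shock.

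| OR | D (g/dL) | Plan's four covariates | Baseline Hb added |
|---|---|---|---|
| 1.11 | 0.5 | 0.21 to 0.44 | 0.03 to 0.25 |
| 1.11 | 1.0 | 0.92 to 0.98 | 0.04 to 0.06 |
| 1.25 | 0.5 | 0.87 to 0.99 | 0.03 to 0.12 |
| 1.25 | 1.0 | 1.92 to 2.04 | 0.02 to 0.06 |

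These agree with the hand calculation. The lowest figure, 0.21, is partly simulation noise: in that setting the estimates were −0.21 without Hb and +0.25 with it, a gap of 0.46, against 0.47 by hand. Adjusting for the four covariates removed almost nothing here (1.92 against 1.96 points unadjusted at D = 1.0, OR 1.25, the lower correlation), because the shift was built to be independent of them. This is the upper end.

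**Two conditions that shrink it** (130 patients per hospital, Hb SD 2 g/dL, D = 1.0 g/dL, OR 1.25, covariates reduced to age and shock):

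- The imbalance comes wholly from a severity that also drives shock. Bias falls from 3.2 points unadjusted to 0.95 with shock in the model, and to −0.09 with Hb as well.
- The set is restricted to Hb below 12 g/dL, approximated by baseline Hb. Bias falls from 1.76 to 1.23 points without Hb in the model, against −0.20 with it.

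**How likely is such an imbalance by chance?** Assume hospital mean Hb varies with SD 0.5 g/dL. The difference between two means of three hospitals has SD 0.5 × √(2/3) = 0.41 g/dL. A gap of 0.5 g/dL or more lies 1.22 SDs out (two-sided probability about 22%). A gap of 1.0 g/dL or more lies 2.45 SDs out (about 1.4%).

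**Against the precision of the trial.** In a companion simulation with Hb SD 2 g/dL and OR 1.25, the SD of the estimate was about 2.5 points. With the 4-df critical value of 2.776, the 95% half-width is 2.776 × 2.5 ≈ 6.9 points. Taking that SD as the standard error, the noncentral t gives a two-sided error rate of about 6% for a bias of 0.9 points and about 10% for 2.0 points, against the nominal 5%.

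**The case against.** The strongest reply is that nothing here is misstated. The covariate list is prespecified, consistent in both places, and made up of plausible prognostic factors. A reader might infer that the plan contradicts itself by checking Hb for selection bias and then not adjusting for it. The documents do not support that. The Rockall and Blatchford scores are also checked and not adjusted for, coagulopathy is adjusted for and not checked, and the plan nowhere says the two lists should match. This part of the objection stands.

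It also stands that Hb being the transfusion trigger does not by itself make it a confounder. Bias needs an imbalance and an association with outcome beyond the four covariates, and the documents quantify neither. The triggers act on Hb during follow-up too, so baseline Hb does not settle who is transfused. The false effect is small beside a half-width of about 7 points, and an imbalance in Hb would be visible in the item 6 comparison.

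The objection does not show that the present list is adequate. Shock and the below-12 restriction each absorb part of an Hb imbalance, but in the checks above neither removed it. Seeing an imbalance in a baseline table is also not the same as having a prespecified estimate that allows for it.

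**Conclusion.** The point holds as a cheap improvement to a secondary analysis. If baseline Hb is imbalanced and prognostic beyond age, shock, co-morbidities and coagulopathy, the adjusted estimate keeps the unexplained part. Illustratively this is 0.2 to 2 percentage points for 0.5 to 1.0 g/dL at odds ratios of about 1.1 to 1.25. The figure rests on an assumed event risk near 10%, assumed slopes, and a shift independent of the other covariates, so smaller values are likely where shock or the Hb restriction takes up some of the difference. By chance alone, an imbalance of 1.0 g/dL would be rare under the assumed spread between hospitals; systematic selective recruitment could produce it, but the documents do not show that it occurred.

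A reader might go further and infer that the headline clinical result is at fault. It is not altered by this covariate list: the main analysis is unadjusted by design, is open to imbalance in any baseline variable, and would be the same with or without the change.

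**What to change.** Add baseline Hb (first recorded value, continuous) to the covariate list under Clinical outcomes and to step 1 under Adjusted analyses. Apply it to the adjusted analyses of further bleeding, all-cause mortality and other outcomes with enough events. Use the within-centre mean imputation already specified for missing covariates. Leave the second stage unchanged: by the plan's own rule in step 5, a patient-level covariate costs no cluster-level degrees of freedom, so the comparison still has six data points and 4 degrees of freedom.

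The cost is one or two more parameters in the first-stage model and no new data. Because sparse outcomes may not bear even that, keep the present list, or use a single linear Hb term, for rare outcomes such as the individual thromboembolic components and acute transfusion reactions. If Hb turns out not to predict the outcome, little is gained and almost nothing is lost.
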